## Background

Alpha-mannosidosis (OMIM 248500) is an ultra-rare monogenic disorder caused by alpha-mannosidase deficiency (Enzyme Commission number: 3.2.1.24) and has an estimated worldwide prevalence of 1:500,000–1:1,000,000 live births [1]. However, as alpha-mannosidosis is an underdiagnosed disease, the real prevalence may be higher [2]. Alpha-mannosidosis is an autosomal recessive, lysosomal-storage disease resulting from mutations in the *MAN2B1* gene, located on chromosome 19 (19 p13.2-q12) [3]. As alpha-mannosidase is a lysosomal enzyme involved in glycoprotein catabolism, reduced activity results in impaired degradation of glycoproteins and leads to an accumulation of mannose-rich oligosaccharides in various tissues [4].

Intracellular accumulation of mannose-rich oligosaccharides leads to different clinical symptoms, including hearing impairment, intellectual disabilities, impairment of motor function and speech development, recurrent infections, immunodeficiency, skeletal abnormalities, destructive polyarthropathy, muscular weakness, ataxia, and psychiatric disease [1]. Alpha-mannosidosis presents in a continuum of clinical symptoms and is a heterogeneous disorder due to the varied manifestations and their different severity, as well as various rates of progression in individual patients [5]. In the majority of patients, the disease is clinically recognized in the first decade of life, progression is slow, and ataxia develops between the ages of 20–30 years [1].

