### Effectiveness variables

Efficacy outcomes to be assessed during routine clinical care are shown in Table 1. For patients under 4 years of age, a 3-min stair climb test (3MSCT) and 2-min walk test (2MWT) are suggested. The forced vital capacity (% volume predicted) is suggested for patients over 4 years of age, and according to the judgment of the treating physician. The proposed schedule of assessments is shown in Table 2, but, again, assessments will be made based on the participating centers’ Standard Operating Procedures.

A global treatment response (GTR) to velmanase alfa will be evaluated in velmanase alfa-naïve patients able to perform the functional tests after 3 years of treatment. The GTR will assess patients in three clinical domains (pharmacodynamic, functional, and QoL) consisting of 1 or > 1 endpoint (Table 3). The pharmacodynamic domain comprises a measure of the accumulated substrate in alpha-mannosidase deficiency, the main pathogenic factor for disease manifestations; a decrease in oligosaccharides is a key biomarker of the pharmacologic effect of the ERT [4]. The second domain includes pulmonary function, endurance, and fine and gross motor proficiency, i.e., all the functional endpoints of the disease [4]. The QoL domain relates to patient-related outcomes of disease burden, disability, and pain [4]. A global response is defined as improvements exceeding the established minimal clinical important difference (MCID) (Table 3) in ≥ 1 endpoint in ≥ 2 of the domains [4]. The MCIDs are derived on the basis of those used in clinical conditions with the highest similarity to alpha-mannosidosis (proxy diseases) [14–17]. Collection of the same effectiveness variables is suggested for patients who are not treated with velmanase alfa, in order to support the description of the natural course of the disease.

**Table 3 Tab3:** Clinical domains, endpoints, and MCID thresholds for the GTR

Domain	Endpoint	Established MCID^a^
Pharmacodynamic	Serum oligosaccharides	Last serum oligosaccharide value ≤ 4 µmol/L
Functional	3MSCT	Improvement ≥ 7 steps/min [14]
	6MWT	Improvement ≥ 30 m [16]
	FVC%	Improvement ≥ 10% [15]
Quality of life	CHAQ DI	Improvement ≤ –0.130 [17]
	CHAQ Pain VAS	Improvement ≤ –0.246 [17]

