### Statistical analyses

Baseline demographic and disease characteristics will be presented by means of descriptive statistics and frequency distributions, as appropriate. Descriptive safety outcomes will be presented and summarized over time. For AEs, both the frequency of patients with an AE and the number of events will be presented by year from baseline. Safety variables will be presented based on person-years at risk. Effectiveness variables will be summarized by means of descriptive statistics or frequency of distribution, as appropriate, and all variables (actual values and change from baseline, if applicable) will be presented by time point. The effects of baseline characteristics on effectiveness will be evaluated by means of regression/logistic models. Covariates in the model will be age (< 18 and ≥ 18 years), sex (male, female), sibships, genotype (Groups 1, 2, and 3, per Borgwardt et al.) [18], residual enzymatic activity (< 10, 10 to < 15, and ≥ 15 nmol/h/mg), and Childhood Health Assessment Questionnaire Disability Index (0–1, 1–2, and 2–3).

Provided that a sufficient number of nontreated patients with adequate data are enrolled, a comparison will be conducted between the velmanase alfa-treated and nontreated groups. Propensity score (PS) analysis will be used to compare GTRs after 3 years; the PS will be calculated as the predicted probability of response using logistic regression, with the same covariates as used for the baseline characteristics regression. Subgroup analyses may be performed depending on overall sample size; results will be presented descriptively.

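### The planned model adjusts genotype for residual enzyme activity and CHAQ-DI, so its genotype coefficient is a conditional association and should not be read as the overall effect of genotype

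*Protocol article*

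**What the plan says.** In the protocol article, Statistical analyses, the aim is put this way: "The effects of baseline characteristics on effectiveness will be evaluated by means of regression/logistic models". One covariate list follows, in a sentence that opens "Covariates in the model will be age" and so refers to a single model. At greater length it reads: "Covariates in the model will be age (< 18 and ≥ 18 years), sex (male, female), sibships, genotype (Groups 1, 2, and 3", with the groups taken from a cited genotype classification, and then "residual enzymatic activity (< 10, 10 to < 15, and ≥ 15 nmol/h/mg), and Childhood Health Assessment Questionnaire Disability Index" in three bands. No separate or sequential model is described, and nothing is said about how an individual coefficient is to be interpreted.

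The Background section describes how the disease arises. It is an "autosomal recessive, lysosomal-storage disease resulting from mutations in the" MAN2B1 gene. Next, "reduced activity results in impaired degradation of glycoproteins and leads to an accumulation of mannose-rich oligosaccharides in various tissues". Finally, "Intracellular accumulation of mannose-rich oligosaccharides leads to different clinical symptoms", among which it lists impaired motor function, polyarthropathy and muscular weakness. CHAQ-DI is not named there. The Effectiveness variables section describes the domain that contains it: "The QoL domain relates to patient-related outcomes of disease burden, disability, and pain".

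**The concern.** A patient's genotype is fixed before residual enzyme activity is expressed. If genotype group influences response partly by determining residual activity, a model that holds activity constant estimates only the part of the genotype association that does not run through activity. The same applies to residual activity if CHAQ-DI lies downstream of it.

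The risk is one of interpretation. Under a stated aim of estimating effects, a small genotype coefficient with a wide interval could be reported as genotype mattering little, when the model has set aside part of the route by which it matters. The Discussion section names disease modifiers among the things the registry will collect, so readers may well look to this table for an answer on genotype.

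**Working it through.** **The plan's own figures.** None bears directly on this point. Table 4 (Study size) is the only design calculation. Its five Clopper–Pearson rows for n = 70 reproduce to three decimals (keeping the non-integer counts 45.5 and 52.5 at proportions 0.65 and 0.75). It is used below only for n = 70 and the response range 0.60 to 0.80.

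**Step 1: the passages side by side.** Background gives the order mutation, reduced enzyme activity, substrate storage, symptoms. Statistical analyses puts the first two of these (as genotype group and activity band) in one model, with a disability score that plausibly reflects the last. Genotype before activity follows from the text. Activity before CHAQ-DI is an inference from the symptom list and the description of the quality-of-life domain.

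**Step 2: how much attenuation could result.** The documents give no path strengths, so all inputs are assumed. Each scenario has 200,000 simulated patients.
- Genotype G = 0, 1, 2, equally likely.
- Activity E = a(G − 1) + standard normal noise, with a = 0.5, 1, 2; Es is E standardised.
- Disability D = −b·Es + √(1 − b²)·noise, with b = 0.3, 0.6, 0.9.
- logit P(response) = 0.8 + d(G − 1) + 0.5·Es − 0.5·D, with d = 0 (no direct path) or d = 0.4 per group.
- E and D are cut into thirds, standing in for the article's bands.

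Model A contains genotype alone; model B contains genotype, E and D. Share remaining = log odds ratio in B ÷ log odds ratio in A, for group 3 versus group 1.

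| Direct path d | Log OR, model A | Log OR, model B | Share remaining | SE ratio, B to A |
|---|---|---|---|---|
| 0 | 0.55 to 1.87 | 0.10 to 0.36 | 13% to 28% | 1.11 to 1.81 |
| 0.4 | 1.24 to 2.65 | 0.86 to 1.16 | 44% to 69% | 1.09 to 1.72 |

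One case worked through, a = 1 and b = 0.6:
- d = 0: 0.14 ÷ 1.10 = 13%; the odds ratio goes from exp(1.10) = 3.0 to exp(0.14) = 1.15.
- d = 0.4: 0.96 ÷ 1.85 = 52%; the odds ratio goes from exp(1.85) = 6.4 to exp(0.96) = 2.6.

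This is not an artefact of the odds ratio's non-collapsibility: adjusting for a predictor that is not a mediator would move the odds ratio away from 1, not towards it.

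**Step 3: does the point depend on CHAQ-DI?** A second simulation (200,000 patients, full mediation, again assumed) uses the article's activity bands. Log activity has SD 0.5 around 12 nmol/h/mg, the logit slope is 1.5 per log unit, and disability is linear in log activity plus noise of SD 0.5. Genotype explains 30%, 50% or 70% of the variance of log activity.

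| Genotype 3 vs 1, odds ratio | 30% | 50% | 70% |
|---|---|---|---|
| Genotype alone | 2.50 | 3.43 | 4.51 |
| Plus activity bands | 1.20 | 1.35 | 1.62 |
| Plus activity and CHAQ-DI bands | 1.18 | 1.32 | 1.58 |

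On the log scale, activity bands alone leave ln 1.20 ÷ ln 2.50 = 0.182 ÷ 0.916 = 20%, then 0.300 ÷ 1.233 = 24% and 0.482 ÷ 1.506 = 32%. Adding CHAQ-DI changes these only to 18%, 23% and 30%. In this set-up nearly all the loss comes from genotype and activity sharing a model, which is the better-supported link.

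**Step 4: precision.** Taking global treatment response as the binary outcome, the list needs 1 + 1 + 2 + 2 + 2 = 8 parameters (age, sex, genotype, activity, CHAQ-DI) before sibships. At n = 70, non-responders number 70 × 0.40 = 28 to 70 × 0.20 = 14, or 28 ÷ 8 = 3.5 to 14 ÷ 8 = 1.75 per parameter. Separating these correlated covariates will be imprecise in any case. This is context, not the finding.

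**The case against.** The strongest reply is that mutual adjustment is standard and legitimate in a prognostic model. The article states no causal estimand and no formal hypothesis testing, and genotype appears in no stated objective. A conditional association answers a different question; it is not an error. This stands, and it is why the planned model should be kept. It does not remove the need to say which question the coefficient answers, because the stated aim is effects and not prediction.

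A second reply is that the article refers to models in the plural and condenses a fuller document, so single-covariate or sequential fits may exist elsewhere. That is possible. The natural reading, though, is that the plural covers linear and logistic forms, since the covariate sentence refers to a single model.

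A third reply concerns the causal premise. A reader might infer that the article itself lays out one chain from genotype through activity to baseline disability and then to response, so that joint adjustment strips genotype of its effect. The documents do not support that. Background explains how the disease arises. It does not say that genotype group grades residual activity among patients, it does not mention CHAQ-DI, and it does not describe how genotype acts on response to velmanase alfa, which itself replaces the enzyme. Removal is also incomplete in every simulated scenario.

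**Conclusion.** The point holds in a limited form. As written, the model gives a genotype coefficient conditional on residual activity, a variable through which genotype probably acts, and that coefficient should not be reported as the overall effect of genotype. The same caution applies to residual activity, on the weaker ground that CHAQ-DI is downstream of it.

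The direction follows from the order of events in Background together with the assumption that the same order matters for treatment response. The size is unknown: the percentages above illustrate assumed path strengths, and the lower range presumes that genotype has no other route to the outcome. It would go too far to conclude that the registry will give a wrong answer on genotype, or that the full model is invalid. Nor does the point carry over to the propensity score, which reuses these covariates: upstream and downstream baseline variables can both be confounders there. This is a cheap improvement to an exploratory analysis.

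**What to change.** Keep the planned model with all listed covariates, including sibships, and state that its coefficients are mutually adjusted (conditional) associations. Add two fits on the same data:
- genotype group with age, sex and sibships, without residual activity and CHAQ-DI;
- residual activity with genotype, age, sex and sibships, without CHAQ-DI.

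The planned model already serves for CHAQ-DI, which on the assumed ordering comes last. Show the estimates side by side with confidence intervals, and say that the ordering is an assumption drawn from the disease mechanism.

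The cost is a sentence or two of analysis wording, two more fits and extra table columns. No further data are needed. The downside is more estimates to read in an exploratory analysis with few non-responders, so all of them should be presented descriptively.

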**Fig. 1 Fig1:**
[figure not shown]
Study design. *VA* velmanase alfa. ^a^If applicable in accordance with routine clinical practice, unscheduled follow-up visits can be performed at, but not limited to, 3 months after VA treatment start, or whenever deemed appropriate according to clinician judgment for patients who start VA treatment within 1 year prior to registry inclusion. ^b^If a patient is transferred to another continuing care site during the 15-year observational period, the new treating site will be formally involved in the registry following a request of authorization submitted to the relevant ethics committee and regulatory authority to complete the 15-year observational period. ^c^Patients can start VA treatment at any time during the course of their participation in the registry; if applicable in accordance with routine clinical practice, the baseline visit should be repeated before administration of VA and unscheduled visits recommended as reported in the schema above

The study will be conducted in accordance with the Declaration of Helsinki, International Council for Harmonisation Good Clinical Practice, Good Pharmacovigilance Practice, and all other applicable laws and regulations of each country in which the research is carried out. The study will also be conducted in accordance with the Strengthening the Reporting of Observational Studies in Epidemiology (STROBE) guidelines. Results of the study will be reported in accordance with the Methodological Standards in Pharmacoepidemiology of the European Network of Centres for Pharmacoepidemiology and Pharmacovigilance (ENCePP) [13]. This is an observational non-interventional study capturing only data from routine clinical practice. Participation in the study will not change the patient–physician relationship, nor influence the physician’s drug prescription or therapeutic or other management of the patient.

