### Study size

As this is an observational study and there is no formal hypothesis testing, the size of the study was conceptualized based on assumed different proportions of GTR in treatment-naïve patients who can perform functional tests after 3 years of treatment. Assuming at least 70 treated patients are enrolled, and assuming a GTR of at least 0.60, the lower limit of the two-sided 95% confidence interval (Clopper–Pearson) is always above 45.0% (Table 4), which is considered a clinically relevant response. Thus, the efficacy analysis is based on a hypothetical treated population of at least 70 patients.

**Table 4 Tab4:** Efficacy analysis based on hypothetical treated population of at least 70 patients

Expected proportion	95% CI lower limit	95% CI upper limit	95% actual width
0.60	0.476	0.715	0.239
0.65	0.527	0.760	0.234
0.70	0.579	0.804	0.225
0.75	0.632	0.846	0.214
0.80	0.687	0.886	0.199

*CI* confidence interval

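### The propensity score for the treated-versus-nontreated comparison is defined as the probability of response (the outcome), not the probability of receiving velmanase alfa

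*Protocol article*

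**What the plan says.** The Statistical analyses section makes the comparison conditional on having enough usable nontreated patients. In that case, it says, "a comparison will be conducted between the velmanase alfa-treated and nontreated groups". The method is then named: "Propensity score (PS) analysis will be used to compare GTRs after 3 years". The score is defined in the same sentence: "the PS will be calculated as the predicted probability of response using logistic regression". The choice of predictors follows by reference to another model: "with the same covariates as used for the baseline characteristics regression".

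That regression is introduced one paragraph earlier: "The effects of baseline characteristics on effectiveness will be evaluated by means of regression/logistic models". Its covariates are age group, sex, sibships, genotype group, residual enzymatic activity and CHAQ Disability Index category. It is an outcome model.

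The Effectiveness variables section groups the GTR endpoints into three domains and fixes what response means: "A global response is defined as improvements exceeding the established minimal clinical important difference (MCID) (Table 3) in ≥ 1 endpoint in ≥ 2 of" them. The Study design section says of participation that it will not alter how patient and physician relate. It adds: "nor influence the physician’s drug prescription or therapeutic or other management of the patient". Treatment is therefore assigned by clinical choice.

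**The concern.** The propensity score is useful because, among patients with the same probability of being treated, the measured covariates have the same distribution in the treated and the untreated. That property belongs to a model of treatment status. A model of response does not have it. It ranks patients by expected outcome and carries no direct information on who was given velmanase alfa.

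Here selection is a live issue. Physicians choose treatment, patients may start at any time during participation, and the Background section says the drug is approved for mild to moderate disease. An analyst who follows the sentence would fit the wrong dependent variable and report the result as adjusted by propensity score. The Statistical analyses section describes no other treated-versus-nontreated effectiveness comparison that could serve as a check.

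**Working it through.** **1. The plan's own figure.** The only design calculation is Table 4, which rests on "Assuming at least 70 treated patients are enrolled, and assuming a GTR of at least 0.60". The Clopper–Pearson limits are Beta(0.025; x, n − x + 1) and Beta(0.975; x + 1, n − x). With n = 70 and x = 0.60 × 70 = 42 they give 0.476 to 0.715, as printed. The other four rows also match to three decimals (the 0.65 and 0.75 rows use x = 45.5 and 52.5). Table 4 is a single-group calculation and makes no use of the score.

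**2. Is there a benign reading of the definition?** Elsewhere in the article (Background, Effectiveness variables, Study size) response means GTR or its components. The covariates are carried over from the effectiveness regression. No section describes a model of treatment assignment. The text may be a slip, but nothing in the article corrects it.

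**3. What a response score does.** Write e(X) for the probability of treatment, and p1(X) and p0(X) for the probability of response with and without treatment. A response model fitted to all patients without a treatment term estimates

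s(X) = e(X)·p1(X) + [1 − e(X)]·p0(X).

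- If treatment has no effect, p1 = p0 and s is a pure prognostic score. If treatment has an effect, s mixes prognosis with selection, and stratifying on it can distort the comparison.
- Under inverse weighting by s, treated patients carry covariate density proportional to f(X)·e/s, and untreated patients f(X)·(1 − e)/(1 − s). These agree only if logit e − logit s is constant, which nothing in the plan ensures.

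**4. Size, by illustration.** All settings are assumptions and none comes from the documents. There are four standard normal covariates, 20,000 patients and 8 runs. The log-odds of treatment are 0.7 + a·X. The log-odds of response are −0.85 + 1.6 × treatment + b·X. The patterns are:

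- Same: a = b = (0.8, 0.8, 0, 0)
- Mixed: a as in Same, b = (0.8, −0.8, 0.8, 0)
- Partial: a as in Same, b = (0.8, 0, 0.8, 0)
- Opposite: a = (−0.8, −0.8, 0, 0), b as in Same

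Stratification uses ten strata. Entries are risk differences.

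| Pattern | True | Crude | Treatment score, stratified | Treatment score, weighted | Response score, pooled, stratified | Response score, pooled, weighted | Response score, untreated-only fit, stratified |
|---|---|---|---|---|---|---|---|
| Same | 0.309 | 0.498 | 0.318 | 0.311 | 0.318 | 0.250 | 0.318 |
| Mixed | 0.286 | 0.288 | 0.285 | 0.285 | 0.235 | −0.125 | 0.285 |
| Partial | 0.308 | 0.404 | 0.314 | 0.310 | 0.277 | 0.130 | 0.315 |
| Opposite | 0.308 | 0.115 | 0.303 | 0.306 | 0.302 | −0.054 | 0.303 |

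Errors of the pooled response score (estimate minus truth):

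- Stratified: +0.009, −0.051, −0.031, −0.006.
- Weighted: −0.059, −0.411, −0.178, −0.362.

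With the treatment coefficient set to 0, the stratified pooled score gave −0.008 to 0.007 and the weighted one −0.427 to 0.002. The one weighted value near zero is the Same pattern, where logit e − logit s = 0.7 + 0.85 = 1.55 is constant, as step 3 predicts.

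A second illustration (two confounders, log-odds of treatment ±0.7 and of response 0.8 per SD, 400,000 patients, true difference 0.214) agrees. The treatment score with weighting gave 0.210 to 0.216. The response score gave 0.20 to 0.22 with quintile stratification and −0.031 to 0.154 with weighting.

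**The case against.** The strongest reply has four parts.

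- **A response score can control confounding.** This stands in part. Fitted in untreated patients only and used for stratification, it is a legitimate prognostic score, and the last column of the table is close to the truth. A reader might infer that the plan offers no control of confounding under any use. That goes too far. But the article calls the score a propensity score and does not state the fitting population that a prognostic score would need.
- **Sign reversal depends on weighting.** This stands. A reader might infer from the weighted figures that the planned comparison would come out reversed. The article never mentions inverse weighting, and how a score is applied is commonly left to the analysis plan, which is not shown. The coefficients are also invented. The figures show that the error can be large under one use, not that it will be.
- **The reach is small.** This stands. The comparison is conditional on enough nontreated patients, and the Study size section says there is no formal hypothesis testing. A reader might infer that the registry's main effectiveness estimate is compromised. The single-group GTR and Table 4 do not use the score.
- **It may be a slip in a condensed article.** Possibly, but what is printed is a definition, not an omission, and it names the wrong dependent variable.

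A reader might also hold that the covariate list is deficient because baseline walking, stair-climb, FVC and oligosaccharide values are absent. The documents do not make that an error. CHAQ Disability Index, itself a GTR endpoint, is already included. The other assessments are not mandatory, and with about 70 treated patients each added, often missing covariate has a price.

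**Conclusion.** The definition is wrong as written: the score models the outcome instead of the receipt of velmanase alfa, so it does not model or balance treatment selection. The comparison of 3-year GTR can be biased as a result. Under the assumed coefficients the bias was little to moderate with stratification on a score fitted without treatment (0.006 to 0.051 in absolute size) and large with inverse weighting (0.059 to 0.411), against true differences of 0.286 to 0.309. These magnitudes are large-sample illustrations and not predictions for the registry. That the definition is wrong does not depend on them. It should be fixed before the comparison is run. It is not critical to the registry, because the analysis is contingent and the single-group results stand.

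**What to change.** Replace the defining sentence in the Statistical analyses section with:

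> The PS is the predicted probability of receiving velmanase alfa (versus not), from a logistic regression of treatment status on the listed baseline covariates, fitted without outcome data.

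If a prognostic score was intended, call it that and state that it is fitted in untreated patients only. Adding baseline functional and oligosaccharide values to the covariates is optional, where completeness and sample size allow.

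The cost is one sentence in the protocol, carried into the analysis plan if that repeats the definition. It needs no new data and changes no stated figure.

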## Methods

### Study design

SPARKLE is a post-authorization safety and efficacy registry in Europe, designed as a multicenter, international, prospective cohort study of patients with alpha-mannosidosis (Fig. 1). The primary objective is to assess the long-term effectiveness and safety of treatment with velmanase alfa under conditions of routine clinical care; secondary objectives include expanding the current understanding of alpha-mannosidosis by collecting data to characterize the natural history of the disease. Source data will be collected by the investigator in the patient file and captured in an electronic case report form (eCRF). This also includes data from patients receiving treatment in a home-care setting. The study, which started patient enrollment in 2020, has an indefinite recruitment period. Patients will be followed for up to 15 years after inclusion. The end of the study is defined as the last visit of the last patient registered in the study. The study will be conducted under conditions of routine clinical practice, according to the treating physician, without mandatory registry assessments. Patients are eligible for the study irrespective of treatment (velmanase alfa, hematopoietic stem cell transplantation or any biologic substance received as part of a clinical trial during participation in the registry).

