### Patient population

Any patient in the European Union with a genetic confirmed diagnosis of alpha-mannosidosis who is willing to participate will be eligible for inclusion. Inclusion criteria are limited to a signed and dated informed consent form, including agreement to permit the Investigator to enter assessment data in the registry that has been recorded prior to inclusion in the registry, which has been obtained from the patient’s medical record. The inclusion form is signed by the patient, parents or a legally acceptable representative according to local regulation. There are no exclusion criteria for patients with this disease. Alpha-mannosidosis and its treatment will progress over the duration of the study and the study protocol may be amended as necessary. Patients’ informed consent will be required for any substantial changes.

Populations for analysis include a velmanase alfa and a no-velmanase alfa safety and efficacy analysis set. The velmanase alfa safety analysis set includes all patients in the registry who have, at some time, received any study drug treatment with a minimum individual follow-up of ≥ 1 month after the last dose. The velmanase alfa efficacy analysis set consists of patients in the same safety analysis set with efficacy evaluations during velmanase alfa treatment and for 12 months thereafter. The no-velmanase alfa safety analysis set includes patients only for the time when they are not, and have not within 1 month, been taking velmanase alfa. The no-velmanase alfa efficacy analysis set includes patients only for the time when they are not, and have not within 12 months, been taking velmanase alfa.

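### The covariates fixed for the treated-versus-nontreated GTR comparison leave out calendar time, so a drift in response without the drug can bias it by an unknown amount in either direction

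*Protocol article*

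**What the plan says.** Under Statistical analyses, if enough nontreated patients with adequate data are enrolled, "a comparison will be conducted between the velmanase alfa-treated and nontreated groups". The method is named: "Propensity score (PS) analysis will be used to compare GTRs after 3 years". The score is defined as a logistic-model prediction of response and is built "with the same covariates as used for the baseline characteristics regression". That list is spelled out: "Covariates in the model will be age (< 18 and ≥ 18 years), sex (male, female), sibships, genotype" group, then "residual enzymatic activity (< 10, 10 to < 15, and ≥ 15 nmol/h/mg), and Childhood Health Assessment Questionnaire Disability Index" class. No calendar year, enrolment period or start date appears in it.

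Other sections bear on calendar time:

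- Study design: enrolment began in 2020 and the study "has an indefinite recruitment period"; each patient is followed for up to 15 years.
- Patient population: "Alpha-mannosidosis and its treatment will progress over the duration of the study". The no-velmanase alfa efficacy set is defined by time off drug, with a 12-month gap after any exposure, so one patient can contribute to both sets.
- Fig. 1, note c: "Patients can start VA treatment at any time during the course of their participation in the registry".
- Baseline and demographic variables: for treated patients, baseline is taken at treatment start, not at registry entry.

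The limitations in the Discussion name variation between centres, self-selection and non-participating centres. They do not name calendar time.

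**The concern.** Calendar time confounds the comparison if two things hold together: the treated and nontreated 3-year windows lie at different dates, and the chance of a response without velmanase alfa changes over those dates. The design leaves room for the first, because a patient who starts the drug during the registry may supply an untreated window followed by a treated one. The article's own expectation that treatment will progress makes the second plausible. None of the listed covariates records the date.

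This is the only controlled effectiveness comparison that the article describes. Because the covariate list is stated, the omission is a choice the document makes, not a detail left to an analysis plan that is not shown.

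**Working it through.** **1. The plan's own figure.** Table 4 gives, for a GTR of 0.60 in 70 treated patients, Clopper–Pearson limits of 0.476 and 0.715. With 42 of 70 responders the limits are 0.4759 and 0.7153, so the row reproduces. It concerns the precision of the treated group alone. The article gives no sample size or power for the treated-versus-nontreated comparison.

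**2. Possible gap within one patient.** A full 3-year untreated window followed by a 3-year treated window, both inside 15 years of follow-up, have starts at least 3 and at most 15 − 3 = 12 years apart. This is the gap for one switching patient, not the gap between the groups.

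**3. Effect of a gap between the groups, with no drug effect.** Inputs: background GTR 0.30 (3 of 10 on placebo, Background section). Assumptions, none given in the documents: g, the yearly odds ratio of response from general care; D, the treated-minus-nontreated difference in mean calendar time, in years. Formula: odds in the treated = (0.30/0.70) × g^D, and GTR = odds/(1 + odds).

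| g | D = 0 | D = 1 | D = 3 | D = 5 |
|---|---|---|---|---|
| 1.05 | 0.300 | 0.310 | 0.332 | 0.354 |
| 1.10 | 0.300 | 0.320 | 0.363 | 0.408 |
| 1.20 | 0.300 | 0.340 | 0.425 | 0.516 |

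The sign reverses if the treated windows lie earlier. With g = 1.10 and D = −3, the odds are 0.4286/1.331 = 0.322 and the GTR is 0.322/1.322 = 0.244.

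**4. Dilution across whole groups, by simulation.** Set-up (all assumed): no drug effect; 70 treated and 40 nontreated windows; nontreated windows start uniformly over years 0 to 10; later starters begin treatment 3 to 8 years after their untreated window starts; other treated windows start uniformly over years 0 to 10; 1,000 runs per setting. Logistic regression on treatment, age class and sex stands in for the propensity analysis, fitted with and without calendar year. Two windows from one patient are treated as independent.

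The mean gap between the groups follows from the set-up. If half of the nontreated windows (20) come from later starters, mean treated time is (20 × 10.5 + 50 × 5)/70 = 6.57 against 5, a gap of 1.57 years. If all 40 do, it is (40 × 10.5 + 30 × 5)/70 = 8.14, a gap of 3.14 years.

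| Nontreated windows from later starters | Gap (years) | Spurious OR, g = 1.10, without / with year | Spurious OR, g = 1.20, without / with year |
|---|---|---|---|
| none | 0 | 1.00 / 1.00 | 1.02 / 1.02 |
| half | 1.57 | 1.17 / 0.99 | 1.37 / 1.01 |
| all | 3.14 | 1.38 / 1.01 | 1.80 / 1.00 |

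The simulated values agree with g^D: 1.10^1.57 = 1.16, 1.10^3.14 = 1.35, 1.20^1.57 = 1.33 and 1.20^3.14 = 1.77. At a nominal 5% level, rejection without the calendar term ranged from 0.036 to 0.260; the top value needs g = 1.20 with every nontreated window from a later starter. With the term it was 0.036 to 0.054. With no drift the odds ratio was 1.01 to 1.05 whether or not year was in the model.

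**The case against.** The case against a strong claim is good, and most of it stands.

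- A reader might infer that treated windows are systematically the later ones, so that general progress in care would be credited to velmanase alfa. The documents do not support a fixed direction. Drug-free time more than 12 months after stopping counts as no-velmanase alfa data. Retrospective records may be entered, and Table 2 anticipates patients who started the drug before inclusion, so treated windows can be early. Open-ended recruitment lets untreated patients enter late.
- A starter supplies an untreated 3-year GTR only after about 3 drug-free years with data, which limits how many do so. The nontreated group could also be read as never-treated patients only. Either way, treated baselines move to treatment start, and concurrency is not assured.
- The sentence on progress explains why the protocol may be amended. It does not say that GTR without the drug will rise. The functional and quality-of-life components are changes from the patient's own baseline, so better care already in place then need not raise them. Milder patients may have less room to improve. Age class, genotype, enzyme activity and CHAQ Disability Index capture part of any shift in case mix.
- A reader might multiply a drift of 2 points a year by an 8-year gap and report 16 points. Neither number has support in the documents, and a gap within switchers overstates the gap between groups, as step 4 shows.
- The comparison is conditional on enough nontreated patients, there is no formal hypothesis testing, and the study size rests on the single-group treated GTR, which is unaffected.

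These points limit size and certainty. They do not supply the missing adjustment: the stated list has no calendar term, and nothing else in the article makes the groups concurrent.

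**Conclusion.** The point holds as an avoidable gap in a stated specification, worth correcting but with limited stakes. The covariates fixed for the treated-versus-nontreated comparison cannot adjust for calendar time, in a registry whose design allows the groups to differ on it. If they differ and response without the drug drifts, the estimate is biased.

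Size and direction are unknown. Under the assumed settings with treated windows later and upward drift, the spurious odds ratio was 1.17 to 1.80 when half or all of the nontreated windows came from later starters, and close to 1 when none did. These figures show that the mechanism works; they are not estimates for this registry. The documents do not support a definite claim that the comparison favours velmanase alfa.

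**What to change.** In Statistical analyses:

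1. Define the propensity score as the probability of receiving velmanase alfa. As written it predicts response, and a calendar term in that model would not by itself balance the groups.
2. Add the calendar year of time zero, as one linear term, to this treatment model and to the outcome regression. Time zero is the baseline from which the 3 years are counted: treatment start for treated windows, and the start of the drug-free window for nontreated ones.
3. Tabulate year of time zero by group, so that readers can see the overlap.
4. As a sensitivity analysis, repeat the comparison using only calendar years in which both groups have time zeros. It should not be the main comparison: where overlap is poor it could drop more than a few patients, which matters in an ultra-rare disease.

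The dates are needed anyway to define the 3-year windows. The cost is one degree of freedom and a small loss of precision. Naming the term before results are seen also avoids the appearance of a data-driven adjustment later.
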